#### **Prostate cancer:**

- High-risk localised (eligible for adjuvant novel anti-androgens), node-positive or metastatic prostate cancer.
- Must have commenced Androgen Deprivation Therapy (ADT) in the form of a gonadotropin-releasing hormone (GnRH) analogue or a GnRH receptor antagonist and/or an androgen receptor antagonist and/or undergone bilateral orchidectomy for prostate cancer. Men must have received last ADT treatment within 12 months of starting the programme or have ongoing treatment-related side effects at the time of commencing the programme if ADT has been discontinued due to toxicity.
- Patients on novel anti-androgen therapy must be stable, and on treatment for at least 3 months, prior to study commencement.
- Patients without histologically confirmed cancer are eligible if both the treating physician and the study PI agree that the patient's history is unambiguously indicative of advanced prostate cancer (e.g. high Prostate-specific antigen (PSA) responsive to ADT in prostate cancer).

#### **Urothelial tract cancer:**

- Stage II – IV urothelial tract cancer (muscle-invasive, node positive or metastatic disease) after completion of primary treatment with systemic therapy (including in the neoadjuvant or adjuvant setting) and/or surgery and recovery from these treatments to a satisfactory level.
- Patients with metastatic disease continuing on maintenance systemic therapy are permitted if they do not have ongoing CTCAE Grade  $>2$  adverse events which will impact their participation at the time of commencing the 12-week programme.

#### **Kidney cancer:**

## The LIAM Mc Trial

- Stage II – III renal cell cancer (clear cell or non-clear cell histologies permitted) after nephrectomy who required and have commenced or completed adjuvant systemic therapy within the past 12 months and have recovered from these treatments to CTCAE Grade  $\leq 2$  or do not have ongoing CTCAE Grade  $>2$  adverse events at the time of commencing the 12-week programme from ongoing systemic therapy.

Or

- Stage IV renal cell cancer (clear cell or non-clear cell histologies permitted) where the participants are continuing on stable dose of maintenance systemic therapy and do not have ongoing CTCAE Grade  $>2$  adverse events at the time of commencing the 12-week programme.

### **Testicular cancer:**

- Stage II-III testicular cancer after completion of primary treatment with systemic therapy and/or surgery within the past 12 months and recovery of all adverse events from these treatments to CTCAE Grade  $\leq 2$ .

### **Penile Cancer:**

- Stage III – IV penile cancer (node positive, recurrent or metastatic disease) after completion of primary treatment with systemic therapy (including in the neoadjuvant or adjuvant setting) and/or surgery and recovery from these treatments to CTCAE Grade  $\leq 2$ .
  - Patients with metastatic disease continuing maintenance systemic therapy are permitted if they do not have ongoing CTCAE Grade  $>2$  adverse events which will impact their participation at the time of commencing the 12-week programme.
6. Participation in other translational or interventional clinical trials is permitted provided the above disease-specific inclusion criteria are met.
  7. Signed consent form by the participant or a legally authorized representative (LAR).

## **4.2 Exclusion Criteria:**

1. Persons who, in the opinion of the researcher or supervising clinician, are unable to cooperate adequately with the study protocol, for example those receiving systemic therapy for a concurrent cancer diagnosis, those with organ system dysfunction which would impact their safe participation in the study, or other uncontrolled medical illness that would impact their safe participation in the study.
2. Patients commencing (in the first 3 months of active systemic therapy) which will impact their ability to participate in the programme are not eligible for the study. These patients may be re-assessed for eligibility when they have completed their therapy or are stable on therapy for at least 3 months.
3. Recent (within 12 months) participation in a study/programme involving a lifestyle intervention (e.g diet, exercise, survivorship).
  - a. Note: Per discretion of PI as to whether may impact the outcome of this study intervention.

### 4.3 The 12-week intervention programme

The programme will involve twice-weekly visits from week 1 – 12 (1 x 1.5 hour session, 1 x 1 hour session). Visits will take place at the Cardiac Rehabilitation Centre in CUH (ARC House, the Mardyke Arena, University College Cork (UCC) or other venues may be used in the event of logistical changes as the study expands from Initial to Expansion Phases).

#### 4.3.1 Screening

A 6-week screening period, to assess eligibility and capture baseline assessments prior to commencing the 12-week intervention programme will involve a screening visit and time for consent. At the Screening visit(s), baseline assessments will include the following:

1. Baseline questionnaire/needs, burden of disease and quality of life assessment
2. Dietetic Evaluation
3. Physiotherapy Evaluation

Information on the questionnaires, evaluations and consent processes are contained in the relevant sections below.

Participants who exceed the 6-week screening period before commencing the 12-week intervention programme may be re-screened for eligibility in a later group. Baseline measurements may need to be repeated if this is the case.

### 4.3.2 The 12-week intervention programme

The 12-week intervention programme will include twice-weekly exercise & assessment sessions for 1-1.5 hour(s). In person visits will be considered optimal, to aid group discussion and peer support, but virtual participation options will be explored as the trial progresses.

The programme referred to here is a guide – sessions may be reordered depending on healthcare professional availability or other factors, as required.

#### 12-week Intervention Programme – Provisional Schedule

Twice weekly visits from week 1 – 12 (1 x 1.5 hour session, 1 x 1 hour session)

|                |                                                                                                                                                                                                                                  |
|----------------|----------------------------------------------------------------------------------------------------------------------------------------------------------------------------------------------------------------------------------|
| Week 1  | Introduction to programme
Individual Baseline assessments (including Nutritional, Physio and Nursing assessments, burden of disease and quality of life experience)
Introduction to signposting to other relevant services |
| Week 2  | Nutrition assessment/education (comprehensive diet history, anthropometric measurements, dietary analysis, individualised dietary advice)                                                                                        |
| Week 3  | Social work education session (Stress management & Psychosocial support)
Nurse present to discuss symptoms                                                                                                                    |
| Week 4  | Nutrition assessment/education (revisit dietary analysis results and adjust tailored advice as appropriate)                                                                                                                      |
| Week 5  | Occupational Therapy (sleep hygiene)
Nurse present to discuss symptom management.                                                                                                                                             |
| Week 6  | Physiotherapy (Fatigue management, pacing strategies, task prioritisation)
Reminder of other available relevant services (Signposting)                                                                                        |
| Week 7  | Nurse led Education session on symptom management of side effects of treatment                                                                                                                                                   |
| Week 8  | Nutrition assessment/education (revisit dietary analysis results and adjust tailored advice as appropriate)                                                                                                                      |
| Week 9  | Pastoral Care (Spirituality & Emotional reasoning)                                                                                                                                                                               |
| Week 10 | Nutrition assessment and education (revisit dietary analysis results and adjust tailored advice as appropriate).                                                                                                                 |
| Week 11 | Final Session to signpost available support services
Nurse present to discuss symptom management                                                                                                                              |
| Week 12 | Final measurements
Patient feedback questionnaires and thank you session                                                                                                                                                      |
| After   | Invitation to Quarterly PPI engagement meetings & PPI Workshops to provide feedback for service improvement                                                                                                                      |
| Month 6 | 6-month follow-up assessment                                                                                                                                                                                                     |

Signposting

- Psychosocial Coaching
- ARC House
- Pharmacist
- Medication Review
- Nursing Review
- Medical Review
- Social Work Supports
- Psych-Oncology
- Supports
- Other, as required

**Note:** These services will be available at all times, with particular signposting and reminder sessions as highlighted in the schedule.

\* Weeks 1-12 will include twice weekly Physio exercise sessions for 1hr

\*\* Visits will take place at the Cardiac Renal Centre Gym in CUH initially, however we are exploring the options of ARC House, the Mardyke Arena, University College Cork (UCC) or other venues for expansion in later phases (see Letters of support).

\*\*\* In person visits will be considered optimal, to aid group discussion and peer support, but virtual participation options will be explored as the trial progresses.

\*\*\*\* Above programme is a guide – Sessions may be reordered depending on healthcare professional availability or other factors, as required.

A series of educational sessions will be incorporated in the programme on a weekly basis, including, but not limited to:

1. Nurse-led education session on symptom management of side effects of treatment
2. Social work education session on stress management & psychosocial support
3. Pastoral care session on spirituality & emotional reasoning,
4. Combined occupational therapy / physiotherapy session on fatigue management, pacing strategies, task prioritisation and sleep hygiene

In addition, regular activities will include:

1. Twice-weekly physiotherapy sessions & plan adjustment
2. 2-weekly dietetics assessment & plan adjustment
3. 2-weekly nursing and psychosocial reviews
4. Signposting to additional available resources including but not limited to
  - a. Psychosocial Coaching
  - b. ARC House
  - c. Pharmacist Medication Review
  - d. Nursing Review
  - e. Medical Review
  - f. Social Work Supports
  - g. Psycho-Oncology Supports
5. Optional weekly psychological coaching in a virtual format via UCC

The order of the planned activities may be switched between weeks (e.g. week 3 and week 4 on the Study Calendar could be swapped due to HCP availability but all 12 weeks of planned activities will happen).

Symptom pathways will be available for common symptoms identified such as joint pain, depression, anxiety, hot flashes, cognitive impairment and fatigue.

Patients will undertake assessments at baseline, 12 weeks and 6 months. Triggers to the study team will prompt symptom evaluation and management in between routine clinic visits. A phone call will take place at 6 months to follow up on progress, symptoms etc.

The candidate ANP will work alongside staff at the Mardyke Arena, UCC; supervised by consultants and supported by a research assistant. This latter position will involve development of educational materials, promotional material, educational events, data collection etc. A research nurse will coordinate research data collection and analysis under the supervision of [name] and the wider research team.

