### 3.3 Primary Study Endpoint:

The primary endpoint of this study is to determine the feasibility and acceptability of introducing a men's cancer survivorship programme into routine follow up care in patients with advanced genitourinary malignancies.

The programme acceptability will be measured with each participant at programme completion and at the 6-month post intervention timepoint. PPI feedback at quarterly engagement meetings will also contribute to understanding the level of acceptability of and support for the study. To determine feasibility of such a multi-disciplinary project, success is multifactorial, and this will be reviewed by the Steering Committee throughout the project and during the scheduled PPI engagement meetings to inform subsequent phases. Qualitative interviews where participant

feedback is provided and the final analysis by the steering and research groups in conjunction with key stakeholders will all contribute to the final determination of the feasibility of the programme. This will help explore what elements of the intervention worked, what elements did not work, and what elements require improvement. A purposefully designed brief feasibility questionnaire will be used in line with previously developed questionnaires by our team [7]. This will be created as part of the scoping review.

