### 3.4 Secondary Study Endpoints:

1. Impact of the survivorship programme on quality of life.
  - EORTC QLQ C30 will be administered at baseline and at the end of the 12-week programme.
  - Quality-adjusted life-year (QALY) (EQ-5D-5L)
  - ASAS-R assessment
  - Additional Assessments as identified by the scoping review will be included in the Expansion Phase.
2. Impact of the survivorship programme on cancer related fatigue.
  - Cancer related fatigue score(EORTC QLQ-FA12).
3. Impact of the programme physiotherapy and dietetic interventions:
  - Maintenance of weight (weight measurement); changes in body composition (lean body mass and fat mass as measured by Bioelectrical Impedance Analysis [BIA]); muscle strength and mass (8 repetition maximum, thigh circumference); physical function and cardiovascular fitness (grip strength, 6 minute walk test [6MWT]).
  - An analysis of body composition analysis using US for muscle mass assessment compared to BIA in a subset of men participating in the study.
  - Changes in dietary intake and diet quality over the study period resulting from the dietetic intervention.
  - Dietary assessments will be conducted by a dietitian. This includes two 24 Hour Dietary Recalls and the WCRF food checklist at baseline and the programme endpoint (12 weeks) and a Food Frequency Questionnaire at baseline and 6 month follow up.
4. Self-care agency and its relationship to quality of life and symptoms experienced.
  - Instruments to measure self-care agency include the ASAS-R
  - Additional Assessments as identified by the scoping review will be included in the Expansion Phase.
5. The resource utilisation of signposted services among participants in the 12-week intervention programme.
  - Quality-adjusted life-year (QALY) (EQ-5D-5L)
  - Resource utilisation (number of signposted resources used). (See section 4.4.4)
6. Satisfaction of participants and Health Care Professionals with the programme and their perceptions of the systems usability.

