##### Survey Questions

The survey will include open-ended questions asking if the participant had any comments about their experience of participating in the intervention/study; elements of the intervention that worked/didn't work and changes they would like to make.

Other process evaluation data will be collected during the study e.g. timing and difficulties experienced with program components, frequency of adverse events (if any), implementation problems. Implementation problems identified during the study will be catalogued as they arise including the mechanisms by which issues are addressed.

Participants will be asked to complete a brief feasibility questionnaire adapted from Zellinger et al (2015) and based on the work of [name] and [name] (both co-applicants) [7], to assess the applicability, acceptability, practicality and relevance of the intervention. The survey will include Likert scale items relating to satisfaction with intervention components.

Qualitative semi structured individual and focus group interviews involving intervention participants and HCPs working within the broader interdisciplinary team will be conducted. The research team including the interventionalists, PPI representatives and key stakeholders (e.g. NCCP representative [name]) will be asked to partake in individual interviews to glean the perspectives of those delivering the intervention and the wider context into which the intervention is delivered.

A semi-structured interview guide will guide an open, in-depth interview with participants about their experience of the trial/intervention, how participants made sense of the intervention, the acceptability of the interventions, their engagement in the processes of the interventions, and the barriers and facilitators encountered.

In addition the interviewer will explore the mechanisms through which the intervention brings about changes which is crucial to understanding both how the effects of the specific intervention occurred and how these effects might be replicated by similar interventions in the future (MRC, 2015).

Context includes anything peripheral to the intervention that may influence its implementation, reach, or its effects. Thus, understanding the context is critical to understanding the potential impact of context on the implementation of the intervention.

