#### **4.4.6 Electronic Patient Reported Outcomes (ePRO) Enrolment and Procedures**

Electronic Patient Reported Outcomes (ePROs) may be used to collect data directly from patients, specifically the quality of life questionnaires and any other self-reported, questionnaire-based tools, using a pseudoanonymised electronic data capture (EDC) system, CASTOR. This service is offered through the Clinical Research Facility-Cork (CRF-C), and meets national and international guidelines with respect to data privacy and protection standards. CRF-C staff will support the development of the ePRO survey template, study database construction and provide investigator training for downstream data collection, monitoring and analyses. Patient names will not be sent to the EDC database.

Patients will be emailed a link to the ePRO Symptom Survey at the specified timepoints (see schedule of activities) during the study period as required. Surveys can be accessed through any standard internet browser. Responses will be immediately uploaded to the study EDC database.

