## The LIAM Mc Trial

|                                                                               |   |   |   |   |   |   |   |   |   |   |   |   |   |   |   |
|-------------------------------------------------------------------------------|---|---|---|---|---|---|---|---|---|---|---|---|---|---|---|
| Signposting to Other Services                                     | X | X | X | X | X | X | X | X | X | X | X | X | X | X | X |
| Social Work Education                                             |   |   |   | X |   |   |   |   |   |   |   |   |   |   |   |
| Nutritional Assessment/Education                                  |   |   | x |   | X |   | x |   | X |   | X |   |   |   |   |
| Occupational Therapy/physiotherapy                                |   |   |   |   |   | X |   |   |   |   |   |   |   |   |   |
| Nurse led education                                               |   |   |   |   |   |   |   | X |   |   |   |   |   |   |   |
| Pastoral care (spirituality & emotional reasoning)                            |   |   |   |   |   |   |   |   |   | X |   |   |   |   |   |
| Usability, Feasibility & Satisfaction Feedback questionnaires    |   |   |   |   |   |   |   |   |   |   |   |   |   | X |   |
| PPI workshop invitation and Invitation to Qualitative Interview  |   |   |   |   |   |   |   |   |   |   |   |   |   | X |   |
| Qualitative Interview (not all participants)                                  |   |   |   |   |   |   |   |   |   |   |   |   |   | X | X |

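### The only scheduled feasibility and satisfaction questionnaires are tied to the week 12 thank-you session, with no required privacy from delivering staff, which risks courtesy bias in the acceptability part of the primary endpoint

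*Protocol*

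**What the plan says.** **Endpoint.** Protocol section 3.3 says that the primary endpoint "is to determine the feasibility and acceptability of introducing a" men's survivorship programme. On timing it says: "The programme acceptability will be measured with each participant at programme completion and at the 6-month post intervention timepoint". It gives no weights and no success threshold. Steering Committee review and PPI feedback also inform the judgement, and the interviews and a final analysis with stakeholders "will all contribute to the final determination of the feasibility of the programme".

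**Instrument.** Section 4.4.4 (Survey Questions) describes a brief feasibility questionnaire, with Likert satisfaction items, whose purpose is "to assess the applicability, acceptability, practicality and relevance of the intervention". Satisfaction and usability on their own are secondary endpoint 6 in section 3.4: "Satisfaction of participants and Health Care Professionals with the programme and their perceptions of the systems usability".

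**Placement.** The provisional schedule in section 4.3.2 lists for week 12 "Patient feedback questionnaires and thank you session". In section 5.0 the row "Usability, Feasibility & Satisfaction Feedback questionnaires" has a single mark, at end of treatment (EoT). Its footnote 10 repeats the week 12 wording.

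**Mode.** Section 4.4.6 says: "Electronic Patient Reported Outcomes (ePROs) may be used to collect data directly from patients". It covers self-reported questionnaires in general, but as an option. Section 4.3.3 and the notes to section 5.0 allow EoT assessments in week 12 or up to 14 days after the programme.

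**The concern.** The men have spent 12 weeks in groups of six with a small team. They are asked to judge that team's programme on an occasion whose other stated purpose is to say thank you. Under such conditions people tend to answer more kindly than they would in private. All participants receive the programme, so there is no second group in which the same tendency would cancel out, and recruiting more men does not reduce it.

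Two uses of the data are exposed. Under section 2.1, a feasible result is to become the basis for offering the programme to all patients as standard care. Under sections 3.3 and 6.1, the study is meant to find out what did not work, and its sample size is set for detecting problems. Reluctance to criticise works against both.

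**Working it through.** **1. The plan's own figure.** Section 6.1 sets 60 men so that a failure occurring 5% of the time is seen with 95% confidence.
- n = ln(1 − 0.95) / ln(1 − 0.05) = 58.4, rounded up to 59. The stated 60 agrees closely.
- At n = 60 the chance of at least one occurrence is 1 − 0.95^60 = 95.4%.
- 12 groups × 6 men = 72, which leaves room for 12 losses (12/72 = 16.7%).

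The sample size is sound and this point does not change it.

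**2. Is the coupling in the operative schedule?** Yes. Section 4.3.2 calls its weekly programme a guide, but footnote 10 puts the same pairing in the Schedule of Activities, on the row for these questionnaires.

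**3. Is there another scheduled administration?** No. The row has one mark, at EoT, and none at the 6-month follow-up. Section 3.3 expects acceptability to be measured at 6 months as well, but the schedule gives no questionnaire for it there. The reading furthest from the farewell therefore cannot be counted on as a check. (That mismatch needs reconciling in its own right.)

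**4. Is separation from delivering staff required?** No.
- Section 4.3.2 has a research nurse coordinate data collection.
- The same section has a research assistant, whose duties include data collection, supporting the candidate ANP.
- Section 4.4.3.1 lists the candidate ANP among those supervising the exercise sessions.

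Delivery and data collection are not clearly kept apart.

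**5. How large could the effect be?** The documents give no rate of courtesy answering and define no binary acceptability rate. Everything in this step is illustration on assumed values.

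*Shift against sampling error.* If true acceptability is p and a fraction c of the men with unfavourable views answer favourably, the observed rate is p + c(1 − p). With p = 70%:

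| c | Observed | Shift (points) |
|---|---|---|
| 10% | 73% | 3 |
| 25% | 77.5% | 7.5 |
| 50% | 85% | 15 |

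- The 95% half-width at n = 60 is 1.96 × √(0.70 × 0.30/60) = 11.6 points.
- The shift reaches that half-width only when c is about 0.116/0.30 = 39%.
- With p = 65% and n = 72 the half-width is 1.96 × √(0.65 × 0.35/72) = 11.0 points. A shift of 10 to 20 points (observed 75% to 85%) would need 10/35 = 29% to 20/35 = 57% of the unfavourable men to change their answer.

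*Detection of problems.* Suppose a problem affects 5% of men, can be seen only through this questionnaire, and a fraction c of those affected do not mention it. The chance of at least one report among 60 men is 1 − (1 − 0.05(1 − c))^60:

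| c | Chance of at least one report |
|---|---|
| 0 | 95.4% |
| 10% | 93.7% |
| 25% | 89.9% |
| 50% | 78.1% |

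Modest reticence costs little on either measure; heavy reticence costs a good deal. The documents do not say which applies.

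**The case against.** The strongest reply is that the setting is inferred. The week 12 line puts two activities side by side and does not say that the forms are filled in during the farewell, in front of the group, or handed to the delivering staff. Section 4.4 invites men to give feedback individually, the EoT window runs for two weeks after the programme, and an emailed form is permitted. The participant leaflet is not at hand and might carry a confidentiality assurance. All of this stands. A reader might infer that the forms must be completed among peers before the professionals being rated, and the protocol does not say so. What remains is that it allows this, points towards it in two places, and requires nothing else.

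A reader might also infer that these questionnaires carry half of the primary endpoint. They do not: no weights are stated, satisfaction is a secondary endpoint, and several other sources feed the determination.

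Criticism also has other routes: open-ended survey items, interviews with up to twenty patients, drop-out forms and a catalogue of implementation problems. These reduce the risk without removing it. The open-ended items sit in a survey of the same kind, the interviews are optional, and PPI feedback is given in a group.

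Finally, moving the forms away from a session may lose some responses. If dissatisfied men are the ones who do not reply, acceptability is again biased upwards. That is a fair warning and shapes the fix.

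**Conclusion.** The point holds as a risk. The single scheduled administration of the questionnaires that measure acceptability is coupled with a thank-you session, and the protocol requires neither private completion nor separation from the delivering staff. This risks inflating the acceptability component of the primary endpoint in a study without a comparator.

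The documents do not show that the result is inflated, and they give no size for the bias. The shifts shown above are illustrations. There is no success threshold for them to cross, so no particular decision can be said to be reversed. The conclusion rests on the wording of the schedule and footnote 10, on the absence of a privacy requirement in the protocol, and on the ordinary expectation that people are kinder in their ratings at a farewell. It is worth correcting because correction is cheap, not because the primary endpoint fails without it.

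**What to change.** - **Section 4.3.2 (week 12) and footnote 10 of section 5.0:** list the questionnaires separately from the thank-you session.
- **Completion:** each man completes the forms alone within the existing EoT window, either by the CASTOR ePRO link or on paper returned to the research nurse at the EoT visit. Send one reminder. In section 4.4.6, make one of these two routes required for these forms.
- **Confidentiality:** state in the protocol that delivering staff will not see individual answers, and tell the men so.
- **Reporting:** give the questionnaire response rate beside the acceptability results, so that any loss of responses is visible.

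**Cost:** protocol wording and one form in a system already planned. The downside is possibly slightly more non-response than in a session where everyone is present. Private paper completion at the EoT visit keeps that small. The sample size and the other assessments are unaffected.
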